### Data collection

2.4

Neonatal patients (1000 cases) diagnosed with hyperbilirubinemia were selected, and 2 ml of blood was collected from the selected persons. Using second-generation high-throughput sequencing technology, 127 deaf-related genes were sequenced from the collected samples. At the same time, physical audiometry was performed on the selected persons and audiometry data were recorded. Genetic test data and physical audiometry data were correlated and analyzed to find the pathogenic loci of hyperbilirubinemia susceptibility to deafness. For those patients with definite symptoms of hyperbilirubinemia and deafness, and no pathogenic loci were detected in 127 genes, blood was collected from these patients, and total exon sequencing was performed to analyze about 22,000 genes and find new pathogenic loci.

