## Introduction

1

Congenital hearing impairment is the most common congenital disease, with an incidence of about 0.1% to 0.3% in healthy newborns and as high as 2% to 4% in high-risk newborns.^[1]^ The most common risk factors for neonatal hearing loss include central infection, neonatal sepsis, hyperbilirubinemia, perinatal asphyxia and hypoxic encephalopathy, preterm delivery, low birth weight, low Apgar score, prolonged mechanical ventilation, and ototoxic agents. Children with hyperbilirubinemia whose serum total bilirubin level reached the blood exchange indicator are one of the common risk factors for hearing loss in children with Neonatal intensive care unit (NICU).^[2]^ The mechanism of hyperbilirubinemia on auditory impairment is not clear. Some scholars believe that hearing loss is a prominent manifestation of bilirubin neurotoxicity.^[3]^ The brain stem auditory pathway is particularly sensitive to the toxic effect of bilirubin.^[4,5]^ High bilirubin levels can even cause permanent damage to nerve development, mainly including deafness and infant cerebral palsy.^[6,7]^

This study protocol will explore the occurrence characteristics of hearing impairment in neonatal children with hyperbilirubinemia, the relationship between serum bilirubin level, unbound bilirubin and the occurrence of hearing impairment, the mutation characteristics of deafness gene in children with hearing impairment, and the difference between deafness gene and normal population.

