### Participants

2.3

A total of 1000 cases of neonatal hyperbilirubinemia were diagnosed in the full-term neonatal ward of Xiamen Children's Hospital from March 2020 to September 2020.

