### Statistical plan

2.5

Excel was used to establish the database, and SPSS 22.0 statistical software was used for statistical analysis in this study.

1.Continuous variable data: for continuous variable data conforming to normal distribution or approximate normal distribution, mean ± standard deviation was adopted to describe the comparison of inter-group differences. When data of continuous variables do not follow normal distribution or variance is uneven, it is expressed as median (quartile spacing) M (P25, P75). Wilcoxon rank sum test in non-parametric test is performed, and multi-independent sample test is performed when there is statistical significance.2.Categorical variables data were described as adoption rate or composition ratio of. Chi-square test was used for comparison of differences between groups, and *P* < .05 was considered statistically significant.3.Logistic regression analysis: physical audiometry results were taken as the dependent variable, and indicators with statistical significance of univariate analysis results were taken as independent variables for binary logistic regression analysis. *P* < .05 was considered as a statistically significant difference.4.ROC curve analysis.

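### Section 2.4 derives 'pathogenic' from the genotype-hearing correlation in the same 1000 infants; chance loci can be reported as pathogenic, and reuse of the label there would be circular

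*Protocol article*

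**What the plan says.** The cohort is a single group (section 2.3): "A total of 1000 cases of neonatal hyperbilirubinemia were diagnosed in the full-term neonatal ward". For each infant, "127 deaf-related genes were sequenced from the collected samples", and hearing is tested at the same time.

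Section 2.4 then says how loci come to be called pathogenic: "Genetic test data and physical audiometry data were correlated and analyzed to find the pathogenic loci of hyperbilirubinemia susceptibility to deafness". The sentence that follows uses the term as a criterion. Infants with definite hyperbilirubinemia and deafness in whom "no pathogenic loci were detected in 127 genes" go on to exome sequencing of about 22,000 genes to find further pathogenic loci.

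The Introduction lists among the objectives "the mutation characteristics of deafness gene in children with hearing impairment", and a comparison of deafness genes with the normal population. In section 2.5 the outcome of the regression is hearing: "physical audiometry results were taken as the dependent variable". Its regressors are chosen by their association with that outcome in the same data: "indicators with statistical significance of univariate analysis results were taken as independent variables for binary logistic regression analysis". The threshold is P < .05, group differences in categorical data are tested by chi-square, and ROC analysis is listed last. The abstract says the loci are meant to guide early screening for deafness genes.

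The gene list is fixed in advance. Which variants in those genes count as pathogenic is not.

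**The concern.** There are two problems, one stated in the text and one conditional.

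**Stated.** Pathogenicity is made the result of an association analysis in the enrolled infants. An association in one cohort, across many loci at P < .05, does not show that a variant causes deafness. Some loci will be associated by chance, and the plan as written would name them pathogenic.

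**Conditional.** If the label produced this way is also the one that defines a positive or negative panel, it depends on the outcome it is then set against. A locus labelled because its carriers happened to be impaired is over-represented among the impaired by construction. An exact and valid P value at the labelling step does not cure this.

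At stake are the share of impaired infants that deafness genes appear to explain, the loci offered for screening and, under the conditional reading, which deaf infants are denied the exome search because a chance locus already counts as their explanation.

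**Working it through.** The article gives no derivation of its 1000, so there is no planned figure to reproduce. The point does not depend on how that number was reached.

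**Inputs from the article.** N = 1000 (2.3); 127 genes (2.4); P < .05 and chi-square (2.5); hearing impairment of 2% to 4% in high-risk newborns (Introduction), hence 1000 × 0.02 to 0.04 = 20 to 40 impaired, with 30 as midpoint.

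**Assumed inputs.** Rare-variant spectrum: 600 variants with 1 carrier, 100 with 2, 30 with 3, 10 with 5 and 5 with 10. That is 745 variants and (600 + 200 + 90 + 50 + 50)/1000 = 0.99 per infant. All are assigned independently of hearing. A locus is labelled if two-sided P < .05 and its carriers are enriched among the impaired.

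**Step 1: chance findings in the scan.** For 127 independent gene-level tests with no true effect, 127 × 0.05 = 6.35 false positives are expected, and the chance of at least one is 1 − 0.95^127 = 99.85%.

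**Step 2: a single carrier is enough.** With K impaired infants, one carrier who is impaired gives Fisher P = K/1000. At K = 30 this is .03, so the locus is labelled. At K = 50 it is .05 and labelling of singletons stops.

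Uncorrected chi-square has no such limit in this range. For a singleton the statistic is 1000 × (1000 − K)/(999 × K). At K = 30 this is 970,000/29,970 = 32.4; at K = 60 it is 940,000/59,940 = 15.7. Both are far beyond the 5% point of 3.84. For a variant with two carriers, one of them impaired, at K = 30 it is 1000 × (1 × 969 − 1 × 29)²/(2 × 998 × 30 × 970) = 15.2, so this is labelled too.

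**Step 3: hand check at K = 30.** Expected labelled singletons are 600 × 30/1000 = 18. The share of impaired infants carrying at least one is 1 − 0.999^600 = 45%. No hearing-pass infant can carry one.

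**Step 4: simulation under no gene effect.**

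| Labelling test and variants | Impaired infants | Impaired carrying a labelled locus | Hearing-pass carrying one |
|---|---|---|---|
| Fisher, all variants | 30 | 47% | 0.2% |
| Fisher, 0.5 to 2 variants per infant | 20 to 40 | 27% to 80% | 0.04% to 1% |
| Fisher, singletons removed | 30 | about 3% | about 0.15% |
| Fisher, all variants | 50 or more | 3% to 5% | 0.1% to 0.2% |
| Chi-square, uncorrected, all variants | 20 to 60 | about 60% | 1% to 2% |

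In the first row about 18.4 loci are labelled, of which about 18.0 are singletons.

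**Step 5: what reuse of the label does to a test.** A separate gene-level model took 127 independent genes, carrier rates of 1% or 3% (assumed) and uncorrected chi-square selection. At least one gene was labelled in 99% to 100% of null runs, and the panel result was then significant against hearing in every such run. The median odds ratio was 7.1 to 11.8 at 2% impaired, 4.6 to 7.4 at 4%, and 3.1 to 5.1 at 10% (10% is an assumption, to allow for screening failures). The apparent AUC was 0.57 to 0.73.

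Carried to an independent cohort of 1000, the same labels gave median odds ratios of 1.03 to 1.19 and AUC about 0.50. With a label fixed before hearing was seen, the median odds ratio was 0.99 to 1.12 and 3% to 6% of runs were significant, close to the nominal 5%.

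**Step 6: the exome gate, if the label is shared.** With 30 impaired infants, all counted as deaf, 0.47 × 30 ≈ 14 would be held back from exome sequencing by chance loci under Fisher, 0.60 × 30 = 18 under chi-square, and about 0.03 × 30 ≈ 1 under Fisher without singletons.

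**The case against.** **The circle is not written down.** The correlation looks for loci of susceptibility across the cohort. The exome gate asks what was found in one patient, and its wording also fits an ordinary laboratory panel report based on known variants. A reader might infer that the plan openly reuses its own correlation result as the panel result. The article does not say that. This stands, and it is why the second half of the point is conditional. It does not remove the need for a change: on that reading one term has two meanings in adjacent sentences, and the first still calls correlated loci pathogenic.

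**No passage plans the biased comparison.** The article does not set carriers of a labelled locus against hearing-pass infants, its stated external comparator is the normal population, and the regression enters indicators that are not named. This also stands. Steps 5 and 6 show what happens if the label is used in that way, not what the plan commits to.

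**The large percentages rest on singletons.** The abstract aims at loci of high frequency, which singletons are not. The 2% to 4% describes congenital impairment in high-risk newborns, while the outcome here may be early screening failure, whose rate is not given. Both are fair, and 47% should not be quoted alone. Against this, the plan's own test is chi-square, and without correction it keeps the figure near 60% up to 60 impaired under the assumed spectrum.

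**Classification criteria belong in a fuller document.** Their absence from an article would be no finding. Here the article does state a route to pathogenicity, and it is the stated route that is at fault. If the full protocol classifies variants without regard to hearing, the article's sentence should be corrected to match.

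**Conclusion.** The point holds in two parts. As written, section 2.4 lets correlation with hearing in one cohort confer the label pathogenic, and section 2.5 applies P < .05 with no stated control over the number of loci. That is a wrong rule, and it needs no assumption about variant frequencies. Circularity in the exome gate, the carrier frequencies, the regression or the ROC curve follows only if the same label is used there. The article offers no other definition, but it does not state the link.

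The direction of the bias is the same in every setting examined; its size is not fixed. It ranges from about 3% to about 80% of impaired infants carrying a chance locus, against at most about 2% of hearing-pass infants. The result depends on the assumed variant spectrum, the choice of Fisher or chi-square, and the number of impaired infants. It would be wrong to conclude that the study will explain about half of its impaired infants by chance: that figure belongs to one setting dominated by singletons.

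The point should be settled before genotype is linked to audiometry, because the label defines a main result and may decide who is sequenced further.

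**What to change.** Rewrite section 2.4 in this order:

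1. Classify every panel variant as pathogenic or likely pathogenic, uncertain, or benign by named published criteria and a dated database version, working on coded samples and blind to audiometry.
2. Lock the list.
3. Link it to hearing. Use only the locked label for the exome gate, the carrier frequencies and the regression.
4. Report loci supported only by correlation in these 1000 infants as associated, not replicated, with multiplicity control.

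The adjustment in item 4 should be applied to exact P values. With the 745 variants assumed above, a Bonferroni threshold is 0.05/745 = 0.00007. A singleton's Fisher P of .03 fails it, but the uncorrected chi-square of 32.4 would still pass. Adjustment alone would not make such a locus pathogenic.

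The cost is protocol wording and a change in the order of laboratory work, with no extra samples or patients. The downside is that fewer loci can be called pathogenic.

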### Statistical plan

2.5

Excel was used to establish the database, and SPSS 22.0 statistical software was used for statistical analysis in this study.

1.Continuous variable data: for continuous variable data conforming to normal distribution or approximate normal distribution, mean ± standard deviation was adopted to describe the comparison of inter-group differences. When data of continuous variables do not follow normal distribution or variance is uneven, it is expressed as median (quartile spacing) M (P25, P75). Wilcoxon rank sum test in non-parametric test is performed, and multi-independent sample test is performed when there is statistical significance.2.Categorical variables data were described as adoption rate or composition ratio of. Chi-square test was used for comparison of differences between groups, and *P* < .05 was considered statistically significant.3.Logistic regression analysis: physical audiometry results were taken as the dependent variable, and indicators with statistical significance of univariate analysis results were taken as independent variables for binary logistic regression analysis. *P* < .05 was considered as a statistically significant difference.4.ROC curve analysis.

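### Unequal variance alone sends a comparison to the Wilcoxon rank-sum test, which as a test of location does not hold 5% when group sizes also differ

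*Protocol article*

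**What the plan says.** The rule is in section 2.5 (Statistical plan), item 1. The rank-based route opens with "When data of continuous variables do not follow normal distribution or variance is uneven". The two conditions are joined by an or, so unequal variance is enough even for a normally distributed variable. Such a variable is then summarised by its median and quartiles and tested as follows: "Wilcoxon rank sum test in non-parametric test is performed, and multi-independent sample test is performed when there is statistical significance".

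Item 3 of the same section defines the logistic model: "physical audiometry results were taken as the dependent variable, and indicators with statistical significance of univariate analysis results were taken as independent variables". The regression is binary, so the hearing outcome used there has two levels. The significance threshold in section 2.5 is .05. The section names no test that allows for unequal variances, and the article does not say how many groups any continuous comparison will have.

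**The concern.** The standard error of the rank-sum statistic is derived on the assumption that both groups have the same distribution. If the spreads differ, that standard error is wrong even when the means and medians are equal. The rule therefore selects the test in a situation where its key assumption is known to fail.

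The error grows with imbalance between groups, and imbalance is plausible here. The study plans 1000 infants, and the Introduction puts congenital hearing impairment at "as high as 2% to 4% in high-risk newborns".

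The relation of serum and unbound bilirubin to hearing impairment is a stated aim, and both are continuous. Their univariate P values decide whether they reach the logistic model. An inflated test can admit a variable that is unrelated to hearing. A test whose error rate is far below 5% can drop one that is related.

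**Working it through.** **Plan's own figure.** The only error rate stated is the .05 level. There is no power, sample-size or familywise figure to reproduce. The check is whether 5% is kept under the rule as written.

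**Inputs**
- Total of 1000 infants (section 2.3).
- Level .05 (section 2.5), taken as two-sided.
- Group split: not given. The 2% to 4% in the Introduction gives 0.02 × 1000 = 20 to 0.04 × 1000 = 40 infants. Assumed range: 20 v 980 to 500 v 500.
- SD ratio r (smaller group over larger): not given. Assumed range: 0.5 to 3.
- Normal data with equal means, so any rejection is a false positive for location.

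**Formula.** Let m be the smaller and n the larger group, ρ1 = r²/(1 + r²) and ρ2 = 1/(1 + r²). Up to a common factor, the variance of the rank-sum statistic is:
- assumed by the test: (m + n + 1)/12
- actual: 1/4 + (n − 1)·arcsin(ρ1)/(2π) + (m − 1)·arcsin(ρ2)/(2π)

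With K = actual/assumed, type I error ≈ 2Φ(−1.96/√K). At r = 1 the two variances agree and the formula returns 5%.

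**30 v 970, r = 2**
- Assumed: 1001/12 = 83.42.
- Actual: 0.25 + 969 × 0.14758 + 29 × 0.03205 = 144.19.
- K = 1.7285, √K = 1.3147, 1.96/1.3147 = 1.491, so the error is 13.6%.

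**30 v 970, r = 0.5**
- Actual: 0.25 + 969 × 0.03205 + 29 × 0.14758 = 35.58.
- K = 0.4266, √K = 0.6531, 1.96/0.6531 = 3.00, so the error is 0.3%.

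**Type I error (%) of the rank-sum test from the formula**

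| Split | r = 0.5 | 0.67 | 1 | 1.2 | 1.5 | 2 | 3 |
|---|---|---|---|---|---|---|---|
| 20 v 980 | 0.2 | 1.2 | 5.0 | 7.3 | 10.3 | 13.8 | 17.6 |
| 30 v 970 | 0.3 | 1.3 | 5.0 | 7.3 | 10.2 | 13.6 | 17.4 |
| 40 v 960 | 0.3 | 1.4 | 5.0 | 7.2 | 10.1 | 13.4 | 17.2 |
| 100 v 900 | 0.7 | 1.8 | 5.0 | 6.9 | 9.4 | 12.5 | 16.0 |
| 300 v 700 | 2.8 | 3.4 | 5.0 | 6.0 | 7.4 | 9.2 | 11.6 |
| 500 v 500 | 5.9 | 5.3 | 5.0 | 5.1 | 5.3 | 5.9 | 6.9 |

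**Simulation check** (3,000 to 6,000 runs per setting; at 5,000 runs the simulation error is about 0.3 points near 5% and 0.5 points near 13%)
- 20 v 980: 12.3% at r = 2, 0.3% at r = 0.5.
- 30 v 970: 13.1% to 14.0% at r = 2 and 0.2% to 0.4% at r = 0.5, over repeated runs.
- 40 v 960: 13.0% and 0.3%.
- 100 v 900: 12.4% and 0.6%.
- 500 v 500: 5.7% to 7.6% with SDs differing two- or threefold.
- Welch's t-test: 4.1% to 6.0% in every setting tried. Brunner-Munzel: 4.3% to 5.5%.

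**Three or more groups.** Kruskal-Wallis has the same weakness. With SDs doubled in the groups of 30, its error is about 10% to 12% at 30/485/485 and 17% to 18% at 30/30/940. It cannot be the remedy when variances differ.

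**The case against.** Several objections carry weight.

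- **The size rests on assumptions.** The article reports no SDs. The 2% to 4% figure is congenital impairment in high-risk newborns, whereas the measured outcome is DPOAE and AABR screening within 48 hours of admission, whose failure rate is not given. With a more even split or similar spreads, the departure is small. This stands, and it is why a range is shown.
- **The rank-sum test is valid for a different null.** As a test of identical distributions it keeps 5%. True, but a rule that invokes it because the variances already differ, and reports medians, is treating it as a comparison of location.
- **Normal data with equal means are stylised.** All infants are selected above the 95th percentile for bilirubin, so values are cut off below, and spread and mean may move together. This limits how literally the percentages apply to bilirubin, but it does not make the rule sound.
- **The univariate tests only screen.** Admitted variables are tested again in the logistic model, and no effect on that final result has been shown. This softens the consequence of a false admission. A variable wrongly dropped gets no second test.

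A reader might also infer that the printed order, rank-sum test first and multi-sample test second, inflates the familywise error. Pairwise tests at .05 taken alone would give at least one false positive in about 11% to 12% of cases with three groups, 20% with four and 29% with five. The article does not support that charge. It defines no comparison of three or more groups, and its only defined hearing outcome is binary. If the multi-sample test must also reject, the error stays at about 4% to 5%. The sentence may also be an awkward rendering of an overall test followed by multiple comparisons. What remains is a request to clarify it.

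**Conclusion.** The point holds for the trigger. Treating "variance is uneven" as sufficient reason for the rank-sum test is a stated rule that does not do what it is meant to do. The error goes up if the smaller group is more variable and down if it is less variable. With 20 to 100 infants in the smaller group, SD ratios from 0.5 to 2 give roughly 0.2% to 14% in place of 5%. At 300 v 700 the range is about 3% to 9%. At 500 v 500 the departure is only upward and modest, about 6% to 8% even with two- to threefold SD differences.

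These figures assume normal data, equal means, and splits and SD ratios that the article does not give. They apply only to variables that the rule actually routes this way. They show that the rule can wrongly admit or drop a bilirubin measure at the screening step, not that it will. No error rate is attached to the order of the two tests.

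**What to change.** In section 2.5, item 1:

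1. Delete unequal variance as a trigger for the rank-sum test. When variances differ between two groups, use Welch's t-test, after log transformation if the variable is skewed, or the Brunner-Munzel test for ordinal or heavily skewed data.
2. Reword the sentence on the multi-independent-sample test. If any comparison has three or more groups, run the overall test first (Welch ANOVA when variances differ, Kruskal-Wallis only when spreads are similar), then Holm-adjusted pairwise tests if it is significant. If every comparison has two groups, delete the sentence.

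The cost is two sentences in the statistical plan. No further data are needed, and Welch's test is available in SPSS, the package the plan names.

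### Section 2.5 judges a search across 127 genes at an unadjusted P < .05, which at the nominal level yields about 6 false gene-hearing associations if no gene matters

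*Protocol article*

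**What the plan says.** Section 2.4 (Data collection) of the protocol article states that "127 deaf-related genes were sequenced from the collected samples" and gives the purpose: "Genetic test data and physical audiometry data were correlated and analyzed to find the pathogenic loci of hyperbilirubinemia susceptibility to deafness". Section 2.3 sets the cohort at 1000 infants.

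Section 2.5 (Statistical plan) gives the rule for categorical variables: "Chi-square test was used for comparison of differences between groups, and *P* < .05 was considered statistically significant". Its third item adds a second step: "indicators with statistical significance of univariate analysis results were taken as independent variables for binary logistic regression analysis". That step has audiometry as the dependent variable and uses P < .05 again.

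No section states a multiplicity adjustment, false-discovery control, a primary gene or a replication sample. The abstract says the loci found are meant to guide early deafness-gene screening in children with hyperbilirubinemia.

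**The concern.** Variant carrier status set against a pass or fail on audiometry is a comparison of two categorical variables. The rule in section 2.5 is therefore the one an analyst would apply to each gene. A 5% threshold limits the false-positive risk of one comparison, but this plan uses it for a discovery search with at least 127. Followed as printed, it can be expected to produce associations even if no gene in the panel affects hearing in these infants.

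The regression step does not repair this. It takes its candidates from the same unadjusted P values, in the same infants, and judges them at .05 again.

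The named test adds a second problem. With few affected infants and rare variants, the chi-square approximation may not hold its 5% level. False associations would then feed into the screening guidance that the study exists to provide.

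**Working it through.** **Plan's own figure.** The only design figure is 1000 infants. It cannot be reproduced, because no effect size, power or event rate is attached to it. No error rate for the whole gene screen is stated either.

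**Inputs**
- Threshold .05 per test (section 2.5).
- 127 genes (section 2.4). The family is larger if several loci per gene are tested.
- 1000 infants (section 2.3).
- Affected infants: the Introduction gives a rate "as high as 2% to 4% in high-risk newborns". Assuming it applies here, that is 20 to 40 of 1000.
- Carriers per gene: not in the documents; 1 to 100 of 1000 assumed.

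**1. Nominal level, independent tests, no true association**
- Expected false positives: 127 × .05 = 6.35.
- At least one: 1 − .95^127 = 99.85%.
- At least three (binomial, 127 tests, .05): 95.6%.

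**2. Weaker assumptions**

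| Setting | Expected | At least 1 | At least 3 |
|---|---|---|---|
| 127 tests, correlation 0.3 (simulated) | about 6.3 | 97% | 74% |
| 127 tests, correlation 0.5 (simulated) | about 6.4 | 83% | 49% |
| 50 testable genes, independent | 2.5 | 92% | – |
| 20 testable genes, independent | 1.0 | 64% | – |

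**3. Does chi-square hold 5% in sparse tables?** With N infants, D affected and K carriers, the number of affected carriers under no association is hypergeometric. The attained size is the total probability of the tables with P < .05.

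- *D = 30, K = 5.* One affected carrier gives chi-square = 1000 × (1×966 − 4×29)² / (30×970×5×995) = 4.99, P = .025. Fisher's P is .14. One or more affected carriers therefore reject, and the attained size is 14.2% for chi-square against 0.8% for Fisher.
- *D = 40, K = 5.* One affected carrier gives 1000 × (1×956 − 4×39)² / (40×960×5×995) = 3.35, below 3.84. Two are needed, and the size is 1.45% for both tests.
- *D = 30, K = 10 and K = 20.* The size is 3.4% and 2.0%, the same as Fisher.

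Over a grid of D = 20, 30, 40 and selected K from 1 to 100, the size runs from about 1.4% to 15%. Over 127 tests that is 127 × .0145 = 1.8 to 127 × .15 = 19 expected false positives. At the low end the chance of at least one is still 84%.

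These are grid values and not strict limits. With D = 30 and K = 6, one affected carrier gives 1000 × (1×965 − 5×29)² / (30×970×6×994) = 3.87, just over 3.84. The size is then 1 − C(970,6)/C(1000,6) = 16.7%.

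**4. Does adjusting the threshold alone suffice?**
- .05/127 = .00039. With exact-level independent tests, the chance of any false positive is 1 − (1 − .00039)^127 = 4.9%, and .05 are expected.
- With chi-square at that threshold, D = 30 and K = 10, the attained size is 0.25% against a nominal 0.039%. Both the threshold and the test need attention.

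**The case against.** The strongest reply is that this is a condensed article. A multiplicity method and an exact-test fallback are often left to a fuller plan, and a general alpha does not exclude them. That would answer a complaint about missing detail. Here the article prints the threshold and the test, uses the threshold twice, and states a discovery aim that they do not suit.

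Other parts of the reply do stand, and they limit the point:

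- **Chi-square for every gene is an inference.** Section 2.5 gives a general rule for categorical variables. No text sets out a gene-by-gene or locus-by-locus test.
- **A reader might infer that several false loci are near certain.** That needs all 127 genes testable, null, close to independent and tested at a true 5%. With Fisher's test the attained size on the grid is about 0.1% to 4.5%, so the expected count could be as low as 0.1.
- **A reader might infer that chi-square P values are always too small in sparse tables.** They are not. The 14.2% example lies near the top of the grid, and moving from 30 to 40 affected infants brings it down to 1.45%.
- **A reader might multiply .05 by the 22,000 genes of the exome step.** Section 2.4 says "total exon sequencing was performed to analyze about 22,000 genes and find new pathogenic loci", but only for deaf infants in whom the panel found nothing. No comparison group or test is described, so neither a false-positive count nor a threshold can be derived.
- **A reader might infer that P < .05 alone makes a locus pathogenic.** The text does not say so. Section 2.4 also speaks of pathogenic loci as something detected, or not, in an individual patient.

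**Conclusion.** The point holds for the 127-gene screen. Section 2.5 states an unadjusted P < .05 for a locus search and reuses it in a regression fed by the same P values. At the nominal level, with independent tests and no true association, about 6 false gene-hearing associations are expected and at least one is near certain (99.85%).

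The exact count is uncertain. It depends on correlation between tests, the number of testable genes and how sparse the tables are. If 20 to 40 infants are affected and 1 to 100 carry a variant in a given gene, the uncorrected chi-square test gives about 2 to 19. Both ranges are assumptions: the 2% to 4% rate is quoted for high-risk newborns in general, and carrier counts are not given.

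The conclusion covers false associations in the panel screen. It does not extend to the exome step or to how a variant is classified as pathogenic.

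**What to change.** Change section 2.5 for the 127-gene screen as follows:

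1. Use Fisher's exact test, or Firth-penalised logistic regression, when expected counts are small.
2. State the family and control it. Use Holm, starting at .05/127 = .00039, or Benjamini-Hochberg at 5% over the 127 genes. If loci are tested instead, the family is all loci tested. The choice of unit can stay with the investigators; pooling carriers within a gene is not required.
3. Label associations that meet only unadjusted P < .05 as hypothesis-generating, including any carried into the logistic regression on that basis.

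This changes wording only and needs no new data. The cost is power per gene and fewer reported loci. As an illustration with assumed carrier rates of 20% in affected and 5% in unaffected infants (normal approximation), going from .05 to .05/127 lowers power from 89% to 61% with 40 affected infants, and from 71% to 37% with 20. Benjamini-Hochberg is generally less costly than Holm, but it controls the proportion of false findings and not the chance of any.
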